## 2.2 Outcome Measures

The primary outcome measure is to evaluate the response rate (RR) of CPI-613 in these patients.

The secondary outcome measures are:

- Safety
- Toxicity
- Progression-free-survival (PFS)
- Overall survival (OS)

## 2.3 Open-Label, Single-Arm Study Design

This is a single-arm open-label study, and investigators and subjects are not blinded to the treatment. Also, the assignment of patients will not be randomized, since there is only a single arm in this study.

# 3.0 PATIENT ELIGIBILITY CRITERIA

## 3.1 Inclusion Criteria

Patients must meet all of the following inclusion criteria before enrollment:

A. Histologically or cytologically proven SCLC that has relapsed or been refractory after at least one line of chemotherapy.

B. ECOG Performance Status of ≤2.

C. Must be ≥18 years of age.

D. Expected survival >1 month.

E. No acute toxicities from previous treatment higher than grade 1 at the start of treatment with CPI-613.

F. Women of child-bearing potential (i.e., women who are pre-menopausal or not surgically sterile) must use accepted contraceptive methods (abstinence, intrauterine device [IUD], oral contraceptive or double barrier device) during the study, and must have a negative serum or urine pregnancy test within 1 week prior to treatment initiation.

G. Men must practice effective contraceptive methods during the study, unless documentation of infertility exists.

H. Laboratory values ≤2 weeks prior to registration must be:

- platelet count ≥100,000 cells/mm^3^ or ≥100 bil/L
- absolute neutrophil count [ANC] ≥1500 cells/mm^3^ or ≥1.5 bil/L
- aspartate aminotransferase [AST/SGOT] ≤3x upper normal limit [UNL]
- bilirubin ≤1.5x UNL
- serum creatinine ≤1.5 mg/dL or 133 µmol/L
- albumin >3.0 g/dL or >30 g/L.

I. Mentally competent, ability to understand and willingness to sign an IRB-approved written informed consent form.

J Have access via central line (e.g., portacath) – double lumen due to CPI-613 administration requirements

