### 5.1.3 Tumor Assessment

Tumor response will be assessed based on RR, and PFS, derived from contrast CT of chest and abdomen and/or PET/CT at baseline and after every two cycles. Contrast CT and/or PET/CT should be performed during week 4, preferably on Wednesday or later (days 3, 4 or 5). RR is the primary endpoint, whereas PFS and OS are secondary endpoints.

According to the Response Evaluation Criteria in Solid Tumors (RECIST), the efficacy of treatment for solid tumors is determined by the tumor size. RECIST criteria are the golden standard to evaluate the tumor. In this study RECIST criteria will be used to evaluate response. However, there is a *pseudoprogression* phenomenon described with the use of CPI-613 in Phase I solid tumor studies (Lee et al. 2012).

It is felt that if CPI-613-induces necrosis of the tumor lesion there may be some radiographic evidence for increasing size. CPI-613 induces tumor necrosis due to its mechanism of action – selectively targeting the altered form of mitochondrial energy metabolism in tumor cells, causing changes in mitochondrial enzyme activities and redox status, which leads to apoptosis, necrosis, and autophagy of tumor cells (Lee et al., 2011; Lee et al., 2012; Senzer et al., 2012; Zachar et al., 2011; Retter et al., 2012).

For the purposes of this study, pseudoprogression will be defined and considered in patients who meet RECIST criteria of progression. It will be the treating physician’s discretion to continue treatment in this situation if the patience is deemed to be getting clinical palliative benefit. In these patients, the study drug can be given for another two cycles prior to making definitive determination of progression or response.

OS will be determined from the first dose of CPI-613 to death, assessed until patient death..Post-study survival, medical and cancer treatment information will be collected bimonthly via telephone contact after treatment termination.

RR is defined as % of patients who experienced a complete response (CR) or partial response (PR). CR and PR are based on Response Evaluation Criteria in Solid Tumor (RECIST) Version 1.1 (Eisenhauer et al. 2009). The best response recorded from the start of the treatment until disease progression (DP) will be considered.

PFS will be determined from the first dose of CPI-613 to DP or death due to any cause.

*5.1.4 Use of pre-study data for analyses*

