# APPENDIX A – REGISTRATION GUIDELINES AND FORMS

The following guidelines have been developed in order to ensure timely registration of your patient.

All patients entered on any CCCWFU trial, whether treatment, companion, or cancer control trial, **must** be registered with the CCCWFU Protocol Registrar or entered into ORIS Screening Log within 24 hours of Informed Consent. Patients **must** be registered prior to the initiation of treatment.

In order to ensure prompt registration of your patient, please:

1. Complete the Eligibility Checklist (attached)
2. Complete the Protocol Registration Form (attached)
3. Alert the WFUHS registrar by phone, *and then* send the signed Informed Consent Form, Eligibility Checklist and Protocol Registration Form to the registrar, either by fax or

e-mail.

Contact Information:

Protocol Registrar [contact]

Protocol Registrar [contact]

Protocol Registrar E-MAIL ([[contact]](mailto:[contact]))

*Protocol Registration is open from 8:30 AM - 4:00 PM, Monday-Friday.

1. Please fax/e-mail ALL eligibility source documents with registration. Patients **will not** be registered without all required supporting documents.

**Note:** If labs were performed at an outside institution, please provide a printout of the results. Please ensure that the most recent lab values are sent.

| **CCCWFU # Eligibility Checklist** | | | | |
| --- | --- | --- | --- | --- |
| **Yes** | **No** | **N/A** | Inclusion Criteria (All responses must be **YES** in order to enter study) | **Eligibility Confirmation (registrar)** |
| 🞎 | 🞎 | 🞎 | 1. Does the patient have histologically or cytologically proven extensive stage SCLC that has relapsed or been refractory after at least one line of chemotherapy. |  |
| 🞎 | 🞎 | 🞎 | 1. Does the patient have an ECOG performance status of < 2? |  |
| 🞎 | 🞎 | 🞎 | 1. Is the patient 18 years of age or older? |  |
| 🞎 | 🞎 | 🞎 | 1. Does the patient have an estimated survival of > 1 month? |  |
| 🞎 | 🞎 | 🞎 | 1. Is the patient free from acute toxic effects from previous treatment superior to grade 1 at the start of treatment with CPI-613? |  |
| 🞎 | 🞎 | 🞎 | 1. If the patient is a woman of child-bearing potential (i.e., pre-menopausal or not surgically sterile), does she agree to use accepted contraceptive methods (abstinence, intrauterine device [IUD], oral contraceptive or double barrier device) during the study, and agree to have a negative serum or urine pregnancy test within 1 week prior to treatment initiation? |  |

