**(Specify)**

| Date of Observation (mm/dd/yy) | |  |  |  |  |  |  |
| --- | --- | --- | --- | --- | --- | --- | --- |
| Cycle: | |  |  |  |  |  |  |
| **TARGET LESIONS** | |  |  |  |  |  |  |
| Response Status (CR, PR, SD, PD) | |  |  |  |  |  |  |
| List sites for response: | Means of Evaluation | Measurement | Measurement | Measurement | Measurement | Measurement | Measurement |
| 1. |  |  |  |  |  |  |  |
| 2. |  |  |  |  |  |  |  |
| 3. |  |  |  |  |  |  |  |
| 4. |  |  |  |  |  |  |  |
| 5. |  |  |  |  |  |  |  |
| 6. |  |  |  |  |  |  |  |
| 7. |  |  |  |  |  |  |  |
| 8. |  |  |  |  |  |  |  |
| 9. |  |  |  |  |  |  |  |
| 10. |  |  |  |  |  |  |  |
| Total sum of LD for all Target Lesions: | |  |  |  |  |  |  |
| **NON-TARGET LESIONS** | | | | | | | |
| Response Status  (CR, Incomplete Response/SD, PD): | |  |  |  |  |  |  |
| List sites for response | Means of Evaluation | Measurement | Measurement | Measurement | Measurement | Measurement | Measurement |
| 1. |  |  |  |  |  |  |  |
| 2. |  |  |  |  |  |  |  |
| 3. |  |  |  |  |  |  |  |
| 4. |  |  |  |  |  |  |  |
| 5. |  |  |  |  |  |  |  |
| 6. |  |  |  |  |  |  |  |
| 7. |  |  |  |  |  |  |  |
| **Observer Signature:** | |  | | | | | |

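### No eligibility criterion requires measurable disease although the primary endpoint is RECIST 1.1 CR+PR, so the response rate can be biased downward

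*Protocol*

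**What the plan says.** **Endpoint.** Protocol Section 2.2: "The primary outcome measure is to evaluate the response rate (RR) of CPI-613 in these patients". Section 5.1.3 agrees: "RR is the primary endpoint, whereas PFS and OS are secondary endpoints". The same section takes RR as the share of patients whose best response is complete or partial, and adds: "CR and PR are based on Response Evaluation Criteria in Solid Tumor (RECIST) Version 1.1". The denominator is patients, with no restriction to those with a lesion that can be measured. Section 9.0 bases the estimate on 20 treated patients.

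**Eligibility.** Section 3.1 is introduced by "Patients must meet all of the following inclusion criteria before enrollment". Its only criterion on the disease itself is A: "Histologically or cytologically proven SCLC that has relapsed or been refractory after at least one line of chemotherapy". The Appendix A eligibility checklist, headed "All responses must be YES in order to enter study", adds extensive stage to that item but says nothing about measurability. The source documentation checklist does not either.

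**Baseline scan.** Section 5.1.1 and Table 5-1 require a CT of chest and abdomen or a PET/CT within 4 weeks before the study. They do not say what it must show.

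**Scoring.** The Appendix G Measurement Form gives target lesions the categories CR, PR, SD and PD, with a row for "Total sum of LD for all Target Lesions". Non-target lesions have only CR, incomplete response/SD, and PD.

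**The concern.** A partial response is a shrinkage in the summed diameters of target lesions. A patient who enters with none has no such sum, and the form offers no other route to PR. One of the two outcomes that make up the primary endpoint is then closed to that patient from the first day, whatever the drug does, while the patient still counts in the denominator.

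The only primary aim of this pilot is a first estimate of RR from 20 patients, so each such patient weighs 5% of the denominator. The effect differs from sampling error: it pushes RR in one direction and could be avoided by an entry criterion. Eligibility is set by the protocol. A statistical analysis plan could choose a denominator, but it could not add an entry criterion, so this is not a detail deferred to that document.

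**Working it through.** **Inputs**

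- n = 20 (Protocol Sections 6.1 and 9.0).
- Two-sided 95% interval, planning rate 0.5, stated maximum distance 0.21 (Section 9.0).
- m, the number of enrolled patients without a target lesion: not in the documents. Assumed range 0 to 5 of 20.
- p, the true RR in patients who have a target lesion: not in the documents. Shown at an assumed 0.20 and at the planning value 0.50.
- c, the CR rate in patients without a target lesion: not in the documents. Set to 0 as the worst case.

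**1. The plan's precision figure.** The Wald half-width is 1.96 × √(0.25/20) = 0.219. The n that gives 0.21 is 1.96² × 0.25 / 0.21² = 21.8, so 22, which is close to 20. At an observed rate of 0.5 and n=20, Wilson gives 0.201, Jeffreys 0.207 and Clopper-Pearson 0.228. The stated 0.21 is thus about right, though slightly optimistic for the Wald and exact intervals. Any Wald figure at smaller n must be compared with 0.219, not with 0.21.

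**2. Can such a patient enter?** Inclusion A to J, the exclusions in Section 3.2, the eligibility checklist and the source documentation checklist were each read for a measurable or target lesion requirement. None has one. Appendix G asks for -1 where an entry does not apply, so a form with no target lesion can be completed.

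**3. Can such a patient respond?** PR: no, because the non-target row lacks it. CR: yes, because the non-target row includes it.

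**4. Patients counted in the denominator.** Expected RR = p × (20 − m)/20 + c × m/20. With c = 0 this is p × (1 − m/20):

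| m | reduction relative to p | p = 0.20 | p = 0.50 |
|---|---|---|---|
| 0 | 0% | 0.20 | 0.50 |
| 1 | 5% | 0.19 | 0.475 |
| 2 | 10% | 0.18 | 0.45 |
| 4 | 20% | 0.16 | 0.40 |
| 5 | 25% | 0.15 | 0.375 |

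Any CR among these patients (c > 0) makes the reduction smaller, so m/20 is its upper bound.

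**5. Patients left out of the denominator.** Wald half-width at 0.5:

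- n = 20: 0.219
- n = 18 (m = 2): 1.96 × √(0.25/18) = 0.231, a rise of 0.012
- n = 16 (m = 4): 1.96 × √(0.25/16) = 0.245, a rise of 0.026

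**6. One data set, two denominators.** With 4 responders, all among patients with target lesions, and m = 4:

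- 4/20 = 20.0% (exact 95% interval 5.7% to 43.7%)
- 4/16 = 25.0% (exact 95% interval 7.3% to 52.4%)

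**The case against.** **A reader might infer that the RR of this trial is biased downward.** The documents do not support that. The bias arises only if patients without target lesions are enrolled and counted, and nothing says how many there would be. In relapsed or refractory disease, with extensive stage required by the checklist, m may be small or zero.

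**A reader might infer that such patients are certain non-responders.** They are not, since the form allows CR for non-target disease. The factor (1 − m/20) therefore gives the lowest expected RR for an assumed m, not the expected value.

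**A reader might infer that these patients would be dropped later and that precision would go from 0.21 to 0.245.** The protocol says nothing about dropping them, and a response-evaluable set may be defined in an analysis plan not seen here. The comparison also mixes methods: like for like, the change is from 0.219 to 0.245, and only if m = 4 were excluded.

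**The effect is small for a descriptive pilot.** At an assumed RR of 20%, m of 2 to 4 shifts the estimate by 2 to 4 percentage points, against an interval of about 22 points either side at the planning rate of 0.5. Section 9.0 tests no hypothesis and sets no threshold that the shift could cross. It also tabulates CR, PR, SD and PD separately. This stands and limits the weight of the point.

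**RR in all treated patients is a coherent quantity.** That is true, and it is why reporting two denominators is an acceptable alternative to a new criterion. It does not answer the main point: as an estimate of how often the drug shrinks tumours, RR in all treated patients is diluted by anyone in whom shrinkage cannot be scored.

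**Conclusion.** The omission is confirmed in every eligibility list of the protocol, and it does not fit the chosen primary endpoint. The consequence is conditional: RR can be biased downward relative to the rate in patients with measurable disease. The relative reduction is at most m/20, which is 0% to 25% over the assumed range of 0 to 5 patients. In absolute terms that is at most 5 percentage points at an assumed true RR of 20%. This rests on assumed values of m and p, on such patients staying in the denominator, and on no CR among them. Excluding them would cost precision instead, again depending on m.

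The point does not invalidate the design, and the shift is small beside the sampling error. It is worth acting on because it concerns the only primary quantity, runs in one direction, and can be removed almost without cost.

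**What to change.** Add to Section 3.1, and as one line in each of the two Appendix A checklists: at least one measurable lesion by RECIST 1.1 on the baseline CT or PET/CT. Use the scan already required and the existing 4-week pre-study window, so that no new procedure or time limit is introduced. The cost is one criterion and two checklist lines, and a few patients become ineligible.

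If the sponsor prefers to keep those patients, define in advance a response-evaluable denominator (patients with a target lesion at baseline) and report RR in it beside RR in all treated patients, each with its 95% interval. This leaves eligibility as it is. The cost is a smaller n and a wider interval for the response-evaluable RR.

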## 3.2 Exclusion Criteria

Patients with the following characteristics are excluded:

A. Patients receiving any other standard or investigational treatment for their cancer, or any investigational agent for any non-cancer indication within the past 2 weeks prior to initiation of CPI-613 treatment.

B. Serious medical illness that would potentially increase patients’ risk for toxicity.

C. Any active uncontrolled bleeding or bleeding diathesis.

D. Pregnant women, women of child-bearing potential not using reliable means of contraception, or lactating women.

E. Men unwilling to practice contraceptive methods during the study period.

F. Life expectancy less than 1 month.

G. Treatment with any anti-cancer therapy within the 2 weeks prior to treatment with CPI-613.

H. Patients with untreated central nervous system (CNS) or epidural tumor.

I. Any condition or abnormality which may, in the opinion of the investigator, compromise his or her safety.

J. Unwilling or unable to follow protocol requirements.

K. Active heart disease including myocardial infarction within previous 6 months, symptomatic coronary artery disease, arrhythmias not controlled with medication, or symptomatic congestive heart failure.

N. Evidence of active infection or serious infection (e.g., septic shock with multi-organ dysfunction) within the past month.

O. Patients with known HIV infection.

P. Requirement for immediate palliative treatment of any kind including surgery.

## 3.3 Inclusion of Women and Minorities

Both men and women and members of all races and ethnic groups are eligible for participation in this trial.

# 4.0 REGISTRATION PROCEDURES

All patients entered on any CCCWFU trial, whether treatment, companion, or cancer control trial, **must** be registered with the CCCWFU Protocol Registrar or entered into the Oncology Research Information System (ORIS) Screening Log within 24 hours of informed consent.

Patients **must** be registered prior to the initiation of treatment.

In order to ensure prompt registration of your patient, please:

1. Complete the Eligibility Checklist (Appendix A)
2. Complete the Protocol Registration Form (Appendix A)
3. Alert the WFUHS registrar by phone, *and then* send the signed Informed Consent Form, Eligibility Checklist and Protocol Registration Form to the registrar, either by fax or e-mail.

Contact Information:

Protocol Registrar [contact]

Protocol Registrar [contact]

Protocol Registrar E-MAIL ([[contact]](mailto:[contact]))

(*Protocol Registration is open from 8:30 AM - 4:00 PM, Monday-Friday.)

1. Please fax/e-mail ALL eligibility source documents with registration. Patients **will not** be registered without all required supporting documents.

**Note:** If labs were performed at an outside institution, please provide a printout of the results. Please ensure that the most recent lab values are sent.

To complete the registration process, the Registrar will:

- assign a patient study number
- register the patient on the study

# 5.0 STUDY PROCEDURES

Table 5-1 (below) provides an overview of the pre-study screen, study procedures for all treatment cycles, and the follow-up period. Specifics are described in subsequent sections.

|  | **Pre-**  **Study^**, a^** | **Every Treatment Cycle*** | | | | | | | **Follow up** |
| --- | --- | --- | --- | --- | --- | --- | --- | --- | --- |
|  |  | **Week 1** | | **Week 2** | | **Week 3** | | **Week 4** |  |
|  |  | **Day 1** | **Day 4** | **Day 1** | **Day 4** | **Day 1** | **Day 4** | **Day 3, 4 or 5** |  |
| Informed consent | X |  |  |  |  |  |  |  |  |
| Demographics | X |  |  |  |  |  |  |  |  |
| Medical history | X |  |  |  |  |  |  |  |  |
| Concurrent meds | X |  |  |  |  |  |  |  |  |
| Physical exam | X |  |  |  |  |  |  |  |  |
| Height, Weight, M^2^ | X |  |  |  |  |  |  |  |  |
| B-HCG^c^ | X |  |  |  |  |  |  |  |  |
| Current symptom evaluation^d^ | X | X |  |  |  |  |  |  |  |
| Vital signs^d^ | X | X | X | X | X | X | X |  |  |
| ECOG Status^d^ | X | X |  |  |  |  |  |  |  |
| Serum chemistry, hematology^b, d^ | X | X |  | X |  | X |  |  |  |
| CPI-613^e^ |  | X | X | X | X | X | X |  |  |
| Efficacy Assessment^f^  Contrast CT of chest / abdomen or PET/CT^f^ | X |  |  |  |  |  |  | X^f^ |  |
| Standard of care MD visit |  | X^h^ |  |  |  |  |  |  |  |
| LDH | X | X |  |  |  |  |  |  |  |
| Adverse event evaluation |  | X |  |  |  |  |  |  |  |
| Phone contact |  | | | | | | | | X |
| * Cycle Length is 4 weeks, with treatment on Days 1 and 4 of Weeks 1 through 3; week 4 is a rest  week (no treatment)  ** The only pre-study data that will be used for data analyses are ECOG status, baseline CT or PET/CT, and LDH. See section 5.1.4 for details.  a: Pre-study requirements must be completed **within** **the following time**  **frames:**  Within **4** weeks: tumor assessments based on contrast CT of chest and abdomen or PET/CT;  Within **2** weeks: medical history, physical exam, vital signs, height, weight, ECOG, evaluation of symptoms and medications, clinical chemistry, hematology, LDH  Within **1** week: pregnancy test for women of childbearing potential  b: Specific chemistries are listed in section 5.2.2. Renal function will be assessed using the Cockcroft-Gault formula.  c: Serum pregnancy test for women of childbearing potential  d: These tests are performed with results available for review within 24 hours before administration of CPI-613  e: CPI-613 is given as a 2-hr IV infusion via a central venous catheter. Treatment with CPI-613 may be adjusted +/- 1 day.  f: Imaging performed while on treatment should be preferably obtained on day 3, 4, or 5 of week 4 during cycles 2, 4,  6 and every two cycles thereafter until progression.  g: Survival and post-study cancer treatment will be monitored bimonthly via telephone contact by the study PA after  patients are taken off of the trial. Phone contact will continue indefinitely.  h: Physical exam and clinical evaluation to be completed within 72 hours prior to treatment with CPI-613 | | | | | | | | | |

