### 5.1.2 Safety Assessment

The safety of CPI-613 will be assessed from the first dose to 1 month after last dose of CPI-613. The assessment will be based on:

- evaluation of symptoms

- vital signs

- ECOG performance status and survival

- clinical chemistry

- renal function

- hematology

The specifics of the safety tests are described in Section 5.2. All safety assessment tests are performed during screening (performed within 2 weeks prior to Cycle 1 treatment with CPI-613. Symptom evaluation and vital signs should be performed prior to each administration of CPI-613. ECOG performance status, clinical chemistries, renal function, and hematology should be performed on day 1 of weeks 1, 2, and 3 for each treatment cycle, with results available for review within 24 hours before administration on day 1 of study drug administration.

###

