The following pre-study tests and evaluations should be documented for future data analysis: ECOG, LDH, and CT (or PET/CT) data.

Pre-study ECOG scores and LDH values will be transferred to the Oncology Research Information System (ORIS) database at the time of registration. All subsequent ECOG scores and LDH values should be recorded on the Efficacy Assessment Form (Appendix D), which will be entered into the corresponding REDCap database. CT or PET/CT data will be recorded on the Measurement Form (Appendix G).

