**List of Adverse Events to be Reported:**

*Abdominal pain

*Alkaline phosphatase

*ALT (SGPT)

*Anorexia

*AST (SGOT)

*Bilirubin (hyperbilirubinemia)

*Calcium (hypercalcemia, hypocalcemia)

*Creatinine

*Diarrhea

*Flushing

*Hemoglobin (anemia)

*Injection site Reaction

*Leukocytes

*Lymphopenia

*Nausea

*Neutrophils (neutropenia)

*Platelets (thrombocytopenia)

*Potassium

*Sodium

*Vomiting

All adverse events should be reported in the AE reporting log (Appendix C) and in ORIS regardless of whether they are on this list. Asterisk (*) denotes expected Adverse Events.

All Serious Adverse Events (SAEs) which are Possibly, Probably or Definitively Related to CPI-613, and Unexpected are required to be reported to Cornerstone Pharmaceuticals via the provided SAE Reporting Form within 7 days. All completed forms must be sent to [name] at Cornerstone. Cornerstone will submit any applicable SAEs to the FDA.

SAE reports must be submitted to Cornerstone by fax or email to the following address:

Department of Regulatory and Clinical Affairs

Cornerstone Pharmaceuticals, Inc.

[name]

[name]

[contact]

Telefax: [contact]

Email: [[contact]](mailto:[contact])

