# 9.0 STATISTICAL CONSIDERATIONS

This is a pilot study with the primary goal to be able to determine initial estimates of response rate (RR), and secondary goals to determine progression-free survival (PFS) and overall survival (OS). Data from this trial will also provide additional data concerning the safety profile of the CPI-613 therapy. We now describe anticipated accrual rates, proposed analyses, and sample size considerations.

Accrual Rate

We anticipate accruing one to two patients per month for this protocol. Thus, we anticipate that we will reach the target sample size of 20 patients treated at MTD within eighteen months.

Proposed Analyses

The analyses for this protocol will be primarily descriptive. With a sample size of 20 treated at MTD, we will be able to get initial estimates of RR, PFS, OS, and safety and toxicity.

For the primary outcome of tumor response rate we will present the proportion of patients who are CR, PR, SD or PD (Complete response, Partial response, stable disease and progressive disease, respectively). In addition, we will estimate the proportion of responders as the percent of patients who are SD, PR and CR, as well as RR (sum of PR + CR) and Disease Control Rate (DCR, which is the sum of SD, PR and CR). For these rates we will also include 95% confidence intervals.

For the time-to-event outcomes, we will estimate survival curves for OS and PFS using Kaplan-Meier techniques. In addition, we will estimate the 6 month and 1-year OS and PFS rates for these participants. We will estimate median overall and progression free survivals for these patients as well. We will also examine safety and toxicities for these 20 patients by looking at each toxicity identified earlier in the protocol by grade.

Sample Size Considerations

Since this is a single arm pilot study, our primary goal is to gather preliminary data on response rates and not to test a specific hypothesis per se. With this sample size we will be able to estimate the response rate using a 2-sided 95% confidence interval with an interval that will extend no more than 0.21 from the observed response rate (if we conservatively assume a response rate of 0.5 for calculations).

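### Screening chemistry, hematology and symptoms are excluded from analysis, so in this single-arm trial pre-existing abnormalities can be counted as toxicity on CPI-613

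*Protocol*

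**What the plan says.** All references are to the protocol.

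- **Restriction on pre-study data.** The double-asterisk footnote, attached to the pre-study column of Table 5-1 (Section 5.0), reads: "The only pre-study data that will be used for data analyses are ECOG status, baseline CT or PET/CT, and LDH". It refers the reader to Section 5.1.4.
- **Section 5.1.4** repeats the list: "The following pre-study tests and evaluations should be documented for future data analysis: ECOG, LDH, and CT (or PET/CT) data". On data flow it adds: "Pre-study ECOG scores and LDH values will be transferred to the Oncology Research Information System (ORIS) database at the time of registration". Imaging goes to the Measurement Form (Appendix G).
- **What is collected.** Section 5.1.2 bases safety on symptoms, vital signs, performance status, chemistry, renal function and hematology, and says: "All safety assessment tests are performed during screening". The safety window runs from the first dose to one month after the last.
- **Who may enter.** Section 3.1 requires: "No acute toxicities from previous treatment higher than grade 1 at the start of treatment with CPI-613". It also sets limits for platelets, neutrophils, AST, bilirubin, creatinine and albumin.
- **What is tabulated.** Section 9.0 will examine safety by "looking at each toxicity identified earlier in the protocol by grade". The toxicities are those in Section 8.1 under "List of Adverse Events to be Reported".

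**The concern.** The footnote is a positive rule about which data enter the analyses. It is not a detail left open for a statistical analysis plan: a plan that used screening laboratory values or symptoms would contradict the protocol.

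The rule also works against the rest of the design. Safety and toxicity are secondary outcome measures (Section 2.2). There is one arm (Section 2.3), so the patient's own pre-treatment state is the natural comparator for a laboratory change. The population has already had chemotherapy, so abnormal values at entry are plausible. A table of grades that ignores baseline can mix abnormalities carried in from disease or earlier treatment with those that arise on CPI-613, which would overstate toxicity.

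**Working it through.** The plan gives no figure of its own on this point. The check is a count, a comparison of sections, and an illustration of scale.

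**1. Count of listed toxicities (Section 8.1).** There are 20 entries.
- Laboratory, 13: alkaline phosphatase, ALT, AST, bilirubin, calcium, creatinine, hemoglobin, leukocytes, lymphopenia, neutrophils, platelets, potassium, sodium.
- Clinical, 7: abdominal pain, anorexia, diarrhea, flushing, injection site reaction, nausea, vomiting.

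Laboratory share: 13/20 = 65%.

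**2. Entry limits for the 13 laboratory items (Section 3.1).**
- With a limit, 5: platelets, neutrophils, AST, bilirubin, creatinine.
- Without a limit, 13 − 5 = 8: alkaline phosphatase, ALT, calcium, hemoglobin, leukocytes, lymphocytes, potassium, sodium.

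Where limits exist they do not all require normal values: AST may reach 3 times and bilirubin 1.5 times the upper normal limit. The Grade 1 ceiling on residual effects of earlier treatment applies to every item, but only to abnormalities caused by that treatment. It does not cap those caused by the disease or another condition.

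**3. Is there another route to a baseline?**
- Table 5-1 schedules symptoms, vital signs, chemistry and hematology on Day 1 of Week 1 of every cycle, with results reviewed within the 24 hours before dosing. In Cycle 1 these are pre-treatment values. They stand in the treatment-cycle columns, so the footnote does not exclude them. No section names them as baseline.
- The adverse event log in the appendices records cycle of onset, start date, grade and attribution. It has no field for baseline grade, and Section 9.0 does not say that onset or attribution will be used.
- Table 5-1 schedules adverse event evaluation on Day 1 of Week 1 and not pre-study. A condition present at entry can therefore first be recorded in a treatment-cycle column.
- The data management table in Section 10.0 lists no form for chemistry or hematology.

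**4. Which grades reach the log?** Section 8.1 asks for all adverse events to be logged. The note at Appendix C limits recording to Grade 3 and above. Under the first rule, Grade 1 and 2 abnormalities present at entry can reach the table. Under the second they do not, and the risk lies mainly in the 8 laboratory items without an entry limit.

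**5. Scale.** With n = 20, one patient whose unchanged abnormality is counted adds 1/20 = 5 percentage points to that row. The documents give no baseline prevalence p, so the values below are assumptions. The expected number of patients is 20p, and the chance of at least one is 1 − (1 − p)^20.

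| Assumed p | Expected patients of 20 | Chance of at least one |
|---|---|---|
| 5% | 1 | 0.64 |
| 10% | 2 | 0.88 |
| 20% | 4 | 0.99 |
| 30% | 6 | >0.99 |
| 50% | 10 | >0.99 |

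These figures show how many patients could bring a given abnormality into the trial. They become toxicity counts only if the abnormality is logged as an event and not set aside.

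**The case against.** The strongest reply is that the information needed is not lost. Cycle 1 Day 1 pre-dose values lie outside the footnote, and start date and attribution, including an unrelated category, are recorded for each event. Section 5.1.4 can also be read as a list for efficacy data capture, since it sends later performance status and LDH to the efficacy form. Treatment-emergent definitions and shift tables are commonly left to a statistical analysis plan. The outcome is secondary, in a 20-patient pilot with mainly descriptive analyses.

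Much of this stands, and it rules out three stronger readings that a reader might infer:

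- *Pre-existing abnormalities will be tabulated as toxicity.* The documents support only that they can be. An event dated before the first dose or marked unrelated could be set aside.
- *A worsening from Grade 1 to Grade 2 cannot be told from a new Grade 2.* The planned summary does not separate them, but pre-dose Cycle 1 values could.
- *The table will be by grade and nothing else.* Section 9.0 says by grade; it does not exclude attribution or onset.

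The reply does not remove the point. The footnote speaks of data analyses without confining itself to efficacy, and a later plan cannot use screening safety data while it stands. The possible remedies exist only as data that someone might choose to use. The conflict over which grades are recorded is a further uncertainty, not a safeguard.

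**Conclusion.** The point holds as a limited one. The protocol requires screening chemistry, hematology and symptoms, then excludes them from analysis. It admits abnormal baselines and examines toxicities by grade with no reference to baseline. Pre-existing abnormalities can therefore be counted as toxicity on CPI-613, with 13 of 20 listed items being laboratory values and 8 of those having no entry limit.

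The size is 5 percentage points per affected patient per row. The total cannot be stated, because it depends on a baseline prevalence that the documents do not give, on which recording rule governs, and on how start date and attribution are used. The direction, if the problem occurs, is overstatement of toxicity. It bears on a secondary outcome only. The response rate, its confidence interval and the sample size are untouched. The change is worth making because it is cheap.

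**What to change.** 1. In the Table 5-1 footnote and Section 5.1.4, either confine the restriction to efficacy analyses or add baseline chemistry, hematology and symptoms to the permitted data.
2. Define the safety baseline as the last value before the first dose, including the pre-dose tests on Day 1 of Week 1 of Cycle 1.
3. In Section 9.0, tabulate worst on-treatment grade against baseline grade for each listed toxicity, and count as treatment-emergent only events that are new or worse than baseline.
4. Reconcile Section 8.1 with the note at Appendix C on which grades are recorded, since this decides what reaches the table.

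Items 2 and 3 could be detailed in a statistical analysis plan, but item 1 has to be changed in the protocol.

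The cost is entry of one baseline laboratory and symptom set for each of 20 patients, and one extra table. The tests are already required, and laboratory reports already go to the registrar with the eligibility documents (Section 4.0 and Appendix A). No additional patient visit or test is needed.
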